## **1.3. Rationale for Dose**

Patients will be randomised in a 1:1:1 ratio to receive either 40mg SB-480848 once daily or 80mg SB-480848 once daily or matching placebo once daily. Single oral doses of up to 100mg have been safe and well tolerated in the 001 study [SHADDINGER]. Repeat doses of up to 80mg have been safe and well tolerated in the 002 study [FINNERTY].

PK/PD modelling has been undertaken to assess the dose/drug concentration/plasma Lp-PLA2 enzyme activity inhibition relationship for SB-480848. Modelling and simulation suggest that peak and trough inhibition of plasma Lp-PLA2 enzyme activity appear to begin to plateau at doses around 80 mg. It is anticipated that once daily doses of 80 and 40 mg SB-480848 are likely to result in approximately 85-90% and 60-65% trough (24-

hour post-dose) plasma Lp-PLA2 enzyme inhibition at steady state, respectively. The level of correlation between plaque and plasma enzyme inhibition is not known, however, this will be investigated in the proposed study.

Modelled data also suggests that steady-state of drug concentration and plasma Lp-PLA2 enzyme inhibition is achieved following 10 days once daily dosing of SB-480848 (half life in man is 25-45 hours). Preclinical data showed significant plaque enzyme inhibition two hours post-dose in Watanabe heritable hyperlipidaemic (WHHL) rabbits following SB-480848 dosing via gavage. This preclinical observation suggests that distribution of SB-480848 into plaque is not a rate-limiting step in the rabbit model. A treatment duration of 14± 4 days is therefore selected in this study.

## **2. OBJECTIVE(S)**

### **2.1. Primary**

- Lp-PLA2 activity in atherosclerotic carotid plaques after 14(+/-4) days treatment with SB-480848, compared to placebo

### **2.2. Secondary**

- To determine the change in Lp-PLA2 activity in blood after treatment with SB-480848
- To determine the change in Lp-PLA2 mass in blood after treatment with SB-480848
- Lp-PLA2 mass in plaque after treatment with SB-480848, compared with placebo
- To evaluate the dose response effects of SB-480848 on plasma and plaque Lp-PLA2 levels
- Levels of defined biomarkers in plaque after treatment with SB-480848, compared with placebo
- To determine the change in levels of defined biomarkers in blood after treatment with SB-480848
- To investigate the correlation between biomarkers and Lp-PLA2 in blood and plaque after treatment with SB-480848
- To characterise the pharmacokinetics (PK) of repeat oral doses of SB-480848 and its metabolite (SB-553253) in this patient population
- To investigate the pharmacodynamics (PD) of SB-480848 following repeat oral administration to this population
- To further investigate the safety and tolerability of SB-480848 through observations of adverse experiences, vital signs, laboratory tests, and effects on 12-lead ECG.
- To determine a change in the oxidised lipids and their metabolites including lyso-PC levels in plasma and in carotid plaques after 14(+/-) days treatment with SB-480848 compared to placebo.

**Pharmacogenetic**

- To determine the variants of candidate genes associated with clinical response to SB-480848
- To determine the variants of candidate genes associated with the absorption, metabolism, distribution and excretion of SB-480848
- To determine the variants of candidate genes associated with tolerability or adverse events experienced during administration of SB-480848

**3. ENDPOINT(S)****3.1. Primary**

- Activity of Lp-PLA2 in atherosclerotic plaque removed during carotid endarterectomy

**3.2. Secondary**

- Mass of Lp-PLA2 in plaque removed during carotid endarterectomy
- Activity and mass of Lp-PLA2 in blood
- Concentrations of the following markers in the plasma/serum:  
Total cholesterol; high density lipoprotein (HDL); low density lipoprotein (LDL); triglycerides; high sensitivity C-reactive protein (hsCRP); CD40 ligand (CD40L); soluble intracellular adhesion molecules (sICAM); E-selectin; plasminogen activating inhibitor type 1 (PAI-1) activity and antigen; matrix metalloproteinase-9 (MMP-9), oxidised lipids and their metabolites including lyso-PC.
- Expression and/or concentration of the following markers in excised plaques:  
CD68 (Macrophages); CD3 (T cells); CD20 or 22 (B cells);  $\alpha$ -actin (smooth muscle cells); CD40L; MMP -2 and -9; PAI -1; ICAM; IL-6; Lp-PLA2 (mRNA expression, oxidised lipids and their metabolites including lyso-PC).

**4. STUDY DESIGN**

A multi-centre, randomised, double-blind, placebo controlled, parallel group study in patients with documented carotid artery disease requiring surgery.

Male or female patients (post-menopausal or using adequate contraception), 35 years of age or above, with planned carotid endarterectomy will be eligible for the study.

Patients will be required to attend the hospital as an out-patient approximately 4 times for study-related procedures. Additionally, study procedures will be conducted on 3 occasions during a patient's planned hospital stay for carotid endarterectomy.

The study consists of 3 parts:

1. **Screen** - at Visit 1, written, informed consent and eligibility assessments will be performed [to be completed in a maximum of 4 weeks prior to randomisation (Visit 2)].
2. **Baseline, Study medication** - baseline assessments and randomisation to one of 2 treatment groups or matching placebo, will occur at Visit 2. At randomisation, patients will be stratified according to statin use and gender. The study medication period is 14 (+/-4) days. Patients will attend one outpatient visit during the 2-week study medication period (Visit 3) and will be telephoned on treatment day 14 if they are to take study medication for longer than 14 days.
3. **Follow-up** - the end of the study medication period will coincide with planned carotid endarterectomy. The last dose of study medication will be taken once a patient has been admitted to hospital during the day prior to surgery, for the purposes of PK and PD sampling (Visit 4). Carotid endarterectomy will take place the next day (Visit 5) according to local institution surgical guidelines. Final PK/PD samples will be taken during the day following surgery (Visit 6). A follow-up visit will occur 2 weeks after the end of study medication (Visit 7).

## 5. STUDY POPULATION

### 5.1. Number of Patients

For 2.5% significance for each comparison to placebo, overall 5% significance, 90% power, a difference between groups equivalent to 50% and between-subject standard deviation on the log scale of 0.7, a sample size of 27 modified intent-to-treat patients is needed per group. Allowing for a 20% rate of dropout or unevaluable plaque 33 patients per group are required, a total of 99 patients.

### 5.2. Eligibility Criteria

#### 5.2.1. Inclusion Criteria

1. Male or female, >35 years of age.
2. Females of childbearing potential (i.e., who are not surgically sterile or postmenopausal with no menstrual period for a minimum of 6 months) during the period of administration of study medication (V2) until completion of follow-up procedures (V7); must be using one of the following contraceptive measures: abstinence OR one of the following methods: documented tubal ligation, documented placement of an intrauterine device (IUD), condom and diaphragm with spermicidal foam/gel/film/cream/suppository, condom with spermicidal foam/film/suppository. Postmenopausal women currently receiving hormone replacement therapy are eligible.
3. Male patients must be willing to abstain from sexual intercourse or use a condom and another form of contraception (eg. IUD, birth control pills taken by a female partner, diaphragm with spermicide) if engaging in sexual intercourse with a women who

could become pregnant between the administration of study medication until completion of the follow-up procedures.

4. Planned carotid endarterectomy within a timeframe compatible with recruitment for the study and able to comply with the requirements of the study, as deemed by the investigator.
5. Written, informed consent to participate.

### **5.2.2. Exclusion Criteria**

A patient will not be eligible for inclusion in this study if any of the following criteria apply:

1. Recent myocardial infarction (within the previous 4 weeks).
2. Currently taking corticosteroids, warfarin, digoxin or a potent CYP3A4 inhibitor (see Section 8.2 Prohibited Medications for details).
3. Recent (<3 months) or ongoing acute infection or significant trauma associated with bruising and/or taking antibiotics. Prophylactic antibiotics for surgery are allowed.
4. Commencement or a change in the dose of a lipid-lowering therapy during the previous 4 weeks from randomisation
5. History of chronic liver disease (e.g. cirrhosis, hepatitis) OR ALT OR AST  $\geq 1.5$  times the upper limit of normal (ULN) at screening.
6. Diagnosis of systemic lupus erythematosus (SLE) or rheumatoid arthritis (RA).
7. Clinically significant anaemia (defined as haemoglobin <11g/dL in males, 10mg/dL in females).
8. History of severe renal impairment (serum creatinine >1.8mg/dL).
9. Unstable angina (Appendix 3).
10. History of asthma (defined as: episode of asthma in the previous 6 months or taking regular anti-asthmatic medication), anaphylaxis or anaphylactoid reactions, severe allergic responses.
11. Abuse of alcohol or drugs within the last 6 months.
12. Any factor or clinical disease state that, in the investigator's opinion, would preclude completion of a safe surgical procedure and/or completion of the study.
13. Use of an investigational drugs within 30 days or 5 half-lives of their last dose prior to starting the study, whichever is the longest.

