#### **10.2.1. Surgery-Related Events or Outcomes Not Qualifying as SAEs**

Carotid endarterectomy is associated with significant morbidity/mortality (risk of stroke, bleeding, death). Such post-operative events will not be recorded as SAEs.

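### Exclusion criterion 7 gives the haemoglobin limit in g/dL for men but in mg/dL for women, so as printed its numeric limit can exclude no woman

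*Protocol*

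**What the plan says.** Criterion 7 in Protocol Section 5.2.2 excludes patients with "Clinically significant anaemia (defined as haemoglobin <11g/dL in males, 10mg/dL in females". The list it belongs to is operative: meeting any one item makes a patient ineligible.

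Four other places bear on how it is read:

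- Section 5.2.1, criterion 1, admits both sexes: "Male or female, >35 years of age". The female limit therefore applies to real patients.
- Section 6.2.4.3 and Appendix 1 have haematology, including haemoglobin, measured at screening by a central laboratory. The parameter list gives no unit and no limit for haemoglobin.
- Section 5.2.2, criterion 8, directly below, uses mg/dL for a different analyte: "History of severe renal impairment (serum creatinine >1.8mg/dL".
- Section 5.2.2, criterion 12, leaves a discretionary exclusion: "Any factor or clinical disease state that, in the investigator's opinion, would preclude completion of a safe surgical procedure and/or completion of the study".

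**The concern.** The male limit carries the unit g/dL; the female limit is printed as "10mg/dL in females". Taken at face value, the second figure is far below any haemoglobin a patient could have, so the half of the criterion that applies to women never operates.

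What is at stake is whether eligibility is decided in the same way everywhere. Each woman screened has a haemoglobin result to be set against this limit. A site that follows the text applies no numeric anaemia limit to women. A site that reads the unit as g/dL applies a limit that the protocol does not state. Both can defend what they did, and checking eligibility against the approved protocol (Section 12.2 asks monitors to verify conduct against it) would give no settled answer.

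**Working it through.** The check is a unit conversion followed by a search for any text that would correct the figure.

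**Inputs** (Section 5.2.2, criterion 7)

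- Male limit: below 11 g/dL.
- Female limit as printed: 10 mg/dL. The less-than sign is carried over from the male limit, which is the ordinary reading of the sentence.

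**Conversion** (1 g = 1000 mg)

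- Female limit in the male unit: 10 / 1000 = 0.01 g/dL.
- Ratio of male to female limit as printed: 11 / 0.01 = 1,100.
- Ratio of the bare figures, ignoring units: 11 / 10 = 1.1.
- Part of the gap due to the unit alone: 1,100 / 1.1 = 1,000.

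Apart from the unit, the two figures are of the same order. This points to a wrong unit rather than a deliberately different limit.

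**Effect on one patient, for illustration only.** Take a woman with a haemoglobin of 9 g/dL. Against the printed limit, 9 > 0.01, so criterion 7 does not exclude her. If the unit is read as g/dL, 9 < 10, so it does. The two readings give opposite eligibility decisions for the same result. The example shows the ambiguity and does not suggest where the limit should lie.

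**Search for a correction.** No other section states a haemoglobin limit. The haematology list in Section 6.2.4.3 names the parameter without a unit. The use of mg/dL in criterion 8 is for serum creatinine, so it neither supports nor corrects the haemoglobin unit, although it is a possible source of the slip.

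**Effect on the statistics.** The sample size inputs in Section 11.4.1 are the between-subject standard deviation, the target inhibition, alpha, power and the dropout allowance. None depends on the haemoglobin limit, and neither does the primary analysis in Section 11.7.1.

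**The case against.** The strongest reply is that the error gives itself away. The sentence defines clinically significant anaemia and pairs two figures of similar size. A limit that no living patient could meet cannot have been intended, and an experienced site would read g/dL. That is probably right, and it makes this a small matter. A plausible but wrong limit would be more dangerous, because nobody would notice it. What the reply does not do is make the text correct: it relies on each site to repair an approved criterion on its own judgement, and nothing in the protocol confirms the repair.

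Two further points on that side stand. The missing inequality sign before the female figure is not a separate defect, since the sign carries over on ordinary reading. And criterion 12 still allows an investigator to exclude an anaemic woman, so it would be wrong to infer that every anaemic woman must be admitted. Only the numeric limit in criterion 7 is inoperative.

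A reader might also infer that women are left exposed to surgical bleeding. The protocol does not support that. It nowhere ties criterion 7 to bleeding, and Sections 6.3.1.1 and 10.1 make clear that the endarterectomy is neither study-specific nor mandated by the protocol. A woman excluded from the trial would still have her planned operation.

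**Conclusion.** The point holds as an error in an operative eligibility threshold. As printed, the female limit is 0.01 g/dL, 1,100 times below the male limit, and the numeric part of criterion 7 works for men only. An anaemic woman could be excluded only through the investigator's discretion in criterion 12.

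This rests on two assumptions: that the less-than sign applies to both figures, and that no living patient has a haemoglobin below 0.01 g/dL. The protocol states neither outright, but neither is in serious doubt. The 1,100-fold ratio measures the misprint. It is not an estimate of how many patients would be wrongly enrolled, and the protocol gives no figures from which to make one.

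Because randomisation is stratified by gender (Sections 4 and 7.5), a reader might suspect a bias between arms. There is no ground for this. The criterion is applied before allocation, the bare figures already differ by sex, and stratification balances the sexes across arms. Sample size, power and the between-arm comparison are unaffected. The correction should be made, but it is a minor one.

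**What to change.** Restate criterion 7 with both haemoglobin limits in one unit and an explicit inequality for each sex. The sponsor should confirm the intended female figure; this review does not propose one. The confirmed wording should then be used unchanged in the screening documents given to sites.

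The cost is one corrected line in the next amendment. No design, sample size or analysis text needs to change.

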### **5.2.3. Other Eligibility Criteria Considerations**

To assess any potential impact on patient eligibility with regard to safety, the investigator must refer to the following document for detailed information regarding warnings, precautions, contraindications, adverse events, and other significant data pertaining to the investigational product being used in this study: Investigator Brochure for SB-480848.

#### **5.2.4. Pharmacogenetics**

Any patient who has given informed consent to participate in the clinical study, has met all the criteria required for entry into the clinical study and receives investigational product may take part in the pharmacogenetic study.

For Patients choosing to participate in the pharmacogenetic study, informed consent must be obtained prior to any blood being taken for this purpose. The informed consent for the PG research must be obtained in addition to the subject's consent to participate in the clinical study. Participation in the PG study is voluntary and refusal to participate will not indicate withdrawal from the clinical study. Refusal to participate will involve no penalty or loss of benefits to which the subject would otherwise be entitled.

No administration of investigational product beyond that detailed in the clinical protocol is associated with the pharmacogenetic study.

### **6. STUDY ASSESSMENTS AND PROCEDURES**

A Time and Events Table is shown in Appendix 1.

Screening procedures should be conducted over a maximum period of 4 weeks prior to Visit 2 (baseline/randomisation).

The visit window for weekly visits is +/- 2 days. Study medication should be taken for 14(+/- 4) days. Visit 5 (day of surgery) must be conducted on the day following the last dose of study medication. Visit 6 must be conducted on the day after surgery, ie. 2 days following the last dose of study medication.

Visit 7 (follow-up) should be conducted 14 days (+/- 3 days) following the last dose of study medication.

#### **6.1. Demographic and Baseline Assessments**

The investigator, or designate, will collect the following data and perform the following procedures for all patients. Informed consent must be obtained from a patient prior to any study-specific procedures taking place.

##### **6.1.1. Demography**

The patient's date of birth, gender and race will be recorded in the CRF.

##### **6.1.2. Medical history/medication**

Relevant medical history (including, but not limited to, reason for carotid endarterectomy and degree of carotid stenosis, cardiovascular events, diabetes) and current medication being taken by the patient, will be recorded in the CRF. Smoking history will also be recorded.

**6.1.3. Physical examination**

The patient's height and weight will be recorded.

**6.2. Safety****6.2.1. Vital signs**

Blood pressure must be measured by the plethysmographic method (with a mercury column sphygmomanometer where available). All measurements will be made on the patient's non-dominant arm supported at heart level, using the same cuff size and the same equipment. If the patient's arm circumference is  $\geq 32$ cm, a large blood pressure cuff should be used. Diastolic blood pressure will be measured at the disappearance of Korotkoff sounds (Phase V). If possible, measurements will be taken by the same staff member and using the same equipment throughout the study.

Blood pressure and heart rate will be measured as follows:

After the patient has sat quietly for at least 5 minutes, blood pressure and heart rate will be measured once. The measurements for sitting heart rate, systolic and diastolic blood pressure will be recorded in the CRF. If the patient is a smoker or uses any tobacco products, a period of 30 minutes without tobacco should be allowed before taking these measurements.

**6.2.2. Electrocardiogram (ECG)**

A standard 12-lead ECG will be recorded at Visits 2 (or at visit 1 if it is logistically easier) and 5. At Visit 5 the ECG can be taken up to 24 hours prior to surgery. If possible, the same equipment should be used throughout the study. A clear copy of the trace must be clearly labelled with patient number, protocol number, centre number and date, it must be signed and dated by the investigator and placed in the CRF. Any clinically significant ECG abnormalities at baseline should be documented in the baseline signs and symptoms section in the CRF. Additional clinically significant ECG abnormalities occurring during the study should be documented on the adverse event forms. ECGs will be reviewed by a core laboratory at the end of the study.

**6.2.3. Chest X-ray**

A chest X-ray will be performed at Visit 1 if one has not been done within the previous 6 months. Any clinically significant abnormalities will be recorded in the Medical History section of the CRF.

**6.2.4. Clinical measurements****6.2.4.1. Haemoglobin A1c, Insulin**

Fasting blood samples will be collected at Visit 2 for determination of glycated haemoglobin and insulin.

**6.2.4.2. Peripheral Lymphocytes**

Blood samples will be collected at Visits 2 and 7 for a microscopic examination of peripheral lymphocytes. Samples will be transferred to Quest Diagnostics and forwarded to a suitably qualified central laboratory. Sample handling and shipping instructions will be provided separately.

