Systemic exposures (AUC and  $C_{max}$ ) achieved during the repeat-dose toxicity studies in rats and dogs were generally higher than exposure in humans at the upper dose proposed for use in the clinical study, although only equivalent or modestly higher at the no effect level in animals (1.0-to 2.4-fold for AUC and 3.9- to 7.8-fold for  $C_{max}$ ). However, given the nature of the findings and the fact that the mild phospholipid accumulation in rats was reversible, it is considered that there are no toxicological implications that would preclude the oral administration of SB-480848 to humans under the conditions of the proposed protocol for the clinical study. As a precaution in this study, blood samples collected at Visits 2 and 5 will be examined for peripheral lymphocytes by electron microscopy, to monitor phospholipid accumulation.

By the end of July 2002, a total of 156 healthy subjects received at least one dose of SB-480848 (dose range 0.5 to 100 mg). Single oral doses of SB-480848 were received by 114 subjects. Of these, 23 subjects also received repeat oral doses of SB-480848 in the 002 study. [FINNERTY] Repeat oral doses of SB-480848 alone and with atorvastatin have been administered to 42 male subjects in study 007. [FINNERTY] SB-480848 is readily absorbed from the gastrointestinal tract. The half life of the compound is approximately 25-45 hours and steady state is achieved in approximately 10 days. SB-480848 is N-deethylated to SB-553253 that is quantifiable in human plasma. SB-480848 has been generally safe and well tolerated. There have not been any serious adverse events (SAEs) reported to date. The most common treatment emergent adverse event (AE) across studies was headache.

Atorvastatin is a lipid-lowering agent metabolized by cytochrome P450 enzyme 3A4 and is a potential concomitant medication in the target population of SB-480848. The pharmacokinetics of SB-480848 and atorvastatin when administered alone and in combination for 10 days were investigated in a parallel group study in 34 healthy adult male subjects (SB-480848/RSD-101PS9/3).

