| Chest X-ray (if one not available within previous 6 months) | ✓                  |                         |          |                                                 |                                   |                         |                                    |
| Fasting blood draw for HbA1c, insulin                       |                    | ✓                       |          |                                                 |                                   |                         |                                    |
| Blood sampling for haematology, clinical chemistry          | ✓                  | ✓                       | ✓        |                                                 | ✓                                 |                         | ✓                                  |
| Blood sampling for peripheral lymphocytes                   |                    | ✓                       |          |                                                 |                                   |                         | ✓                                  |
| 12-lead ECG                                                 |                    | ✓           |          |                                                 | ✓                     |                         |                                    |
| Concomitant medication                                      | ✓                  | ✓                       | ✓        |                                                 | ✓                                 |                         | ✓                                  |
| Physical examination, vital signs                           | ✓                  | ✓                       | ✓        |                                                 | ✓                                 |                         | ✓                                  |
| Baseline signs and symptoms/Adverse events                  | ✓                  | ✓                       | ✓        |                                                 | ✓                                 |                         | ✓                                  |

Continued

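### The lymphocyte check for phospholipid accumulation is promised for Visit 5 in Section 1.1 but scheduled only for Visit 7, 10 to 16 days later and off drug

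*Protocol*

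**What the plan says.** Three places in the protocol set the timing of the peripheral lymphocyte examination.

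- Section 1.1 (Background), closing its discussion of toxicology and exposure margins, says as a precaution that "blood samples collected at Visits 2 and 5 will be examined for peripheral lymphocytes by electron microscopy, to monitor phospholipid accumulation".
- Section 6.2.4.2, the procedure section, says: "Blood samples will be collected at Visits 2 and 7 for a microscopic examination of peripheral lymphocytes".
- Appendix 1 (Section 14.1), in the row "Blood sampling for peripheral lymphocytes", has ticks under Visits 2 and 7 only. The Visit 5 cell is empty.

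Section 6 sends sites to that table ("A Time and Events Table is shown in Appendix 1") and fixes the two visits relative to dosing: "Visit 5 (day of surgery) must be conducted on the day following the last dose of study medication", and "Visit 7 (follow-up) should be conducted 14 days (+/- 3 days) following the last dose of study medication".

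Section 1.1 also gives the pharmacokinetics ("The half life of the compound is approximately 25-45 hours and steady state is achieved in approximately 10 days") and states that, compared with human exposure at the upper dose, exposure in the toxicity studies was "only equivalent or modestly higher at the no effect level in animals (1.0-to 2.4-fold for AUC". It describes the phospholipid accumulation seen in rats as mild and reversible, clearing within a month of stopping treatment.

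**The concern.** Section 1.1 and the operative schedule cannot both be right, and the two visits answer different questions. A sample on the day after the last dose shows whether accumulation is present at the end of dosing. A sample about two weeks later shows only whether any accumulation has persisted off drug.

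Sites following Section 6.2.4.2 and Appendix 1 would take no end-of-dosing sample. For a change that the protocol itself calls reversible, a normal result at Visit 7 fits two histories: accumulation never occurred, or it occurred and regressed. The result could then be read as reassurance that it does not provide. An ethics committee reading Section 1.1 would also believe that an end-of-dosing check is in place when the schedule does not deliver one.

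**Working it through.** No sample size, power or alpha figure is involved. The check compares the three texts and then works out what the difference in timing means.

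**Inputs**

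| Input | Value | Source |
|---|---|---|
| Post-dose lymphocyte visit, Background | Visit 5 | Section 1.1 |
| Post-dose lymphocyte visit, procedures | Visit 7 | Section 6.2.4.2 |
| Post-dose lymphocyte visit, schedule | Visit 7 | Appendix 1 |
| Timing of Visit 5 | last dose + 1 day | Section 6 |
| Timing of Visit 7 | last dose + 14 days, ± 3 | Section 6 |
| Half-life | 25–45 hours | Section 1.1 |

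**Gap between the visits**

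- Visit 7 falls between 14 − 3 = 11 and 14 + 3 = 17 days after the last dose.
- Visit 7 minus Visit 5 is 11 − 1 = 10 to 17 − 1 = 16 days (nominally 14 − 1 = 13).

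**Half-lives elapsed** (hours since last dose ÷ half-life, taking Visit 5 as 24 hours after the dose)

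- Visit 5: 24/45 = 0.53 to 24/25 = 0.96.
- Visit 7: (11 × 24)/45 = 264/45 = 5.87 to (17 × 24)/25 = 408/25 = 16.32.

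**Drug level remaining** (0.5 raised to the number of half-lives; simple exponential decline is an assumption)

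- Visit 5: 0.5^0.96 = 51% to 0.5^0.53 = 69%.
- Visit 7: 0.5^16.32 = 0.001% to 0.5^5.87 = 1.7%.

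Visit 5 therefore samples a patient who is still exposed, and Visit 7 one who is essentially off drug. These percentages describe drug level only. The protocol gives no rate at which accumulation regresses in human lymphocytes. For rats it gives only an upper bound of one month, and the rat study listed in Section 13 had a one-month off-dose period. The chance of missing accumulation at Visit 7 therefore cannot be calculated.

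**The case against.** The strongest reply is that the operative text is consistent. Section 6.2.4.2 and Appendix 1 agree on Visits 2 and 7, sites face no conflicting instructions, and one sentence in Background is out of line. Visit 7 may have been deliberate, and nothing in the protocol settles that. On this view the contradiction supports only a wording correction, and a sample at all three visits is a design preference.

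The safety context can also be read more mildly. Section 1.1 reports a Cmax margin of 3.9 to 7.8-fold at the no-effect level alongside the narrower AUC margin. It places the rat accumulation at 30 mg/kg/day and above, finds nothing of toxicological importance at 10 mg/kg/day, and concludes that dosing is acceptable. No stopping rule depends on the lymphocyte result. The one-month bound is compatible with accumulation still being visible at days 11 to 17, and the half-life arithmetic does not measure regression. Finally, the 11 to 17 day interval applies to patients on the planned schedule. Those who withdraw after randomisation attend an early-withdrawal version of Visit 7 (Section 9.2.1), for which no such interval is given.

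Most of this stands as a limit on the claim: the intended visit is unknown, and a missed finding is possible but not shown. It does not remove the contradiction. If Visit 7 was intended, Section 1.1 misdescribes the precaution. If Visit 5 was intended, the schedule fails to carry it out. Nor is the choice of visit neutral, because the acceptability argument in Section 1.1 itself leans on reversibility, and reversibility is what makes a single late sample ambiguous.

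**Conclusion.** The concern holds. The current text contradicts itself on when the post-dose lymphocyte sample is taken, and under the schedule sites would follow, that sample comes 10 to 16 days later than Section 1.1 states: day 11 to 17 after the last dose instead of day 1. In half-lives this is 5.9 to 16.3 against 0.5 to 1.0, using the stated 25 to 45 hours and a nominal 24 hours at Visit 5. As scheduled, the check can detect accumulation that persists off drug but not accumulation that was present at the end of dosing and has since reversed.

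This should be corrected. It weakens a named safety precaution but does not touch the primary endpoint, the sample size, the analysis or any dosing decision.

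**What to change.** Add a peripheral lymphocyte sample at Visit 5 in Section 6.2.4.2 and in Appendix 1, taken with the haematology and chemistry draw already planned at that visit (Section 6.2.4.3). Keep the Visit 7 sample as a check on reversibility and to cover patients who withdraw after randomisation. Change Section 1.1 to name the same visits. While doing so, use one description of the method, since Section 1.1 specifies electron microscopy and Section 6.2.4.2 says only that the examination is microscopic.

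The cost is wording in three places, plus one tube and one examination per patient (up to 99), with no extra visit. Handling on the day of surgery must be confirmed, because Section 6.2.4.2 leaves handling to separate instructions.

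If the sponsor intended Visit 7 alone, the minimum change is to correct Section 1.1 and state that, for patients on the planned schedule, the check covers only accumulation still present 11 to 17 days after the last dose. That costs wording only.
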